### Randomization and Blinding

We will use computer-generated block randomization to ensure balance (1:1) between the two treatment groups. Randomization codes will be provided via text message directly to the blinded researcher’s password-protected phone line with a secure online backup. This will occur for enrollment as each participant signs the consent form. All study participants will complete baseline assessments before randomization, and follow-up assessments will occur through online surveys with the survey links delivered via text messaging or email messaging depending on which study arm participants belong to. Participants will be asked to use either the email address or phone number with which they receive messages as their study ID on the follow-up online surveys.

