### Intervention and Implementation Strategies

eHealth approaches have been rapidly expanding in recent decades, with evidence indicating that the provision of internet-based mental health services is clinically effective [23] and cost-effective even though many health professionals have, until quite recently, been slow to engage in this clinical domain [24,25]. Supportive text messages have also become increasingly accepted as an appropriate and acceptable means of delivering psychological care to patients with mental health issues [26]. It is estimated that 99% of received text messages are opened, and 90% of all text messages are read within 3 minutes of reception [27], presenting an accessible opportunity to close the psychological treatment gap for patients with depression [28]. In 3 randomized controlled trials conducted in Ireland [29] and Canada [30], patients with MDD who received twice-daily supportive text messages had significantly greater reductions in their depression symptom scores than patients who received treatment as usual. In the first of the 2 studies conducted in Ireland, after 3 months, the mean difference in Becks Depression Inventory-II (BDI-II) scores between the intervention and control groups was –7.9 (95% CI –13.06 to –2.76, Cohen *d*=0.85) in favor of the intervention group [29]. Similar results were reported in another Irish study with a larger sample size and, after 3 months of exposure, a Canadian study reported a significant difference in mean BDI-II scores for the intervention versus control groups (mean 20.8, SD 11.7 vs mean 24.9, SD 11.5, respectively; *F*_1,60_=4.83, *P*=.03, *η*_p_^2^=0.07) with an effect size (Cohen *d*) of 0.67 [30]. A recent literature review of studies conducted on the effectiveness of text messaging as an adjunct therapy for mothers with postpartum depression living in low-income countries also reported a positive outcome [31], where the mothers showed a preference for receiving psychological care via text messaging [32]. Several studies reported high user satisfaction with a supportive text message intervention [28,33], and in one of these studies, 83% of subscribers to the Text4Mood program reported that daily messages contributed to improving their overall mental well-being [28].

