### Inclusion Criteria

The inclusion criteria are as follows:

Persons aged 18 to 65 years who have the capacity to provide informed consent;Patients who have been assessed using structured clinical interviews for DSM-5 and diagnosed with an MDD;Patients who have a mobile phone with an active line and a functional email address and can access both email messages and text messages;Patients who willingly agree to be enrolled in the trial and sign the consent form.

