#### Data Collection

Participants who provide informed written consent and agree to participate in the study will be asked to complete a baseline assessment questionnaire that captures both demographic and clinical information. At 6, 12, and 24 weeks, an online survey link will be sent to participants via email or text messages along with an invitation for them to complete the assessments. Participants will enter the email address or phone number through which they receive the messages as their study identifier at the start of the survey so that their data at the 4 time points can be matched. Participants who have not completed their follow-up assessments within 3 days of the due date will be contacted by a research coordinator and reminded to do so, or if they require assistance to complete the assessment, such assistance will be offered, including the option to complete the assessment over the telephone. In instances where such assistance is required, a blinded research assistant will be asked to read out the survey questions to the participant and record their responses.

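### Follow-up survey links travel by the randomised channel and the study ID is that channel's address, so outcome response may differ by arm and the ID may unmask the telephone assistant

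*Protocol article*

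**What the plan says.** Randomization and Blinding has follow-up "survey links delivered via text messaging or email messaging depending on which study arm participants belong to". The same section fixes the identifier: "Participants will be asked to use either the email address or phone number with which they receive messages as their study ID". Effectiveness Evaluation, Data Collection, repeats this and places the step at the opening of the questionnaire: "Participants will enter the email address or phone number through which they receive the messages as their study identifier at the start of the survey". The stated purpose is to link the four time points.

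That Data Collection section also provides a fallback in both arms: "Participants who have not completed their follow-up assessments within 3 days of the due date will be contacted by a research coordinator". The channel of this contact is not given. Patients who need help may complete the survey by telephone, and then "a blinded research assistant will be asked to read out the survey questions to the participant and record their responses".

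Under Inclusion Criteria, every participant must have a working mobile line and email address and "can access both email messages and text messages". Ethics and Dissemination describes the outcomes as self-completed online scales. Table 1 draws dose received and fidelity (reading of messages) from survey questionnaires, but dropout from subscription data. Satisfaction is also collected by questionnaire (Implementation Evaluation, Data Collection).

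**The concern.** The channel being compared is also the route by which the outcome is requested. A patient who ignores the daily emails is likely to overlook an emailed survey link too, and likewise for texts, possibly at a different rate. Missing outcomes would then be tied to engagement with the assigned strategy, and the amount missing could differ between arms.

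The direction matters because the question is whether email is noninferior. If patients who do not respond are doing worse, and email loses more of them, the email responders look better than the email arm as a whole, and the comparison leans toward a noninferiority conclusion. The survey-based satisfaction and reading measures pass through the same filter.

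The identifier raises a second, smaller issue. An email address points to the email arm and a phone number to the text arm. A survey record that opens with this identifier sits badly with an assistant described as blinded who records answers in it.

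**Working it through.** **The plan's own figure.** Sample Size gives 80 evaluable patients and at most 20% dropout overall: 80 / (1 − 0.20) = 100, which reproduces the recruitment target, 50 per arm. The 20% is not split by arm.

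**Bias formula.** Let q be the proportion of an arm with no outcome, and g the amount, in SD, by which non-responders score worse than responders (taken as equal in both arms, and as what remains after baseline adjustment). The full-arm mean is the responder mean plus q × g in the worse direction. Subtracting the arms, the responder difference departs from the full-arm difference by

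shift in favour of email = (q_email − q_text) × g.

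The document gives neither q by arm nor g, so both are assumptions. Keeping 20% missing overall and ignoring the fallback:

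| Non-response, text / email | g = 0.25 SD | g = 0.5 SD | g = 1.0 SD |
|---|---|---|---|
| 20% / 20% | 0 | 0 | 0 |
| 15% / 25% | 0.10 × 0.25 = 0.025 | 0.10 × 0.5 = 0.05 | 0.10 × 1.0 = 0.10 |
| 10% / 30% | 0.20 × 0.25 = 0.05 | 0.20 × 0.5 = 0.10 | 0.20 × 1.0 = 0.20 |

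If text loses more patients, or non-responders do better, the sign reverses.

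**Precision.** The standard error of the difference, in SD, is √(1/n_text + 1/n_email).
- 40 and 40 evaluable: 0.2236
- 42.5 and 37.5: 0.2240
- 45 and 35: 0.2254

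Unequal response costs almost no precision. The issue is bias, which a larger sample would not cure.

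**Does the missing-data rule repair it?** Addressing Missing Data specifies mean substitution and excludes questionnaires with more than 20% of responses missing.
- A wholly missing survey exceeds that limit. Excluding it leaves the responder comparison above.
- Substituting the arm mean reproduces the responder difference.
- Substituting the overall mean shrinks a responder difference of 0.5 SD to 0.394 SD at 10% / 30%. Almost all of this comes from the substitution itself, since 20% / 20% gives 0.40 SD.

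None of these restores the patients lost through the channel.

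**Identifier.** Three statements stand side by side: the ID is the address or number of the assigned channel; it is entered at the start of the survey; and, in assisted cases, a blinded assistant records the responses. No arm-neutral ID is described. If the assistant handles or sees that first field, the arm can be inferred. This reaches telephone-assisted assessments only.

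**The case against.** The strongest reply is that the plan already limits the loss. Both arms get the same coordinator contact and telephone option, and because the contact channel is not stated it cannot be assumed to be tied to the arm. Addressing Missing Data adds active engagement of patients at risk of loss and near real-time monitoring, and Table 1 records delivery failures. This stands: the table above describes the position before these steps, and what survives them is unknown. They do not remove the risk, because the coordinator acts only after a link has gone unanswered, and the mix of online and telephone completion may itself differ by arm.

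Four stronger readings are tempting and are not supported.
- A reader might infer that outcomes are captured solely through the randomised channel. The telephone option rules that out.
- A reader might infer that the dropout comparison becomes one of survey delivery. Table 1 takes dropout from subscription data, and a patient who misses a link remains subscribed.
- A reader might take the Introduction's statement, "It is estimated that 99% of received text messages are opened", as proof that email response will be lower. The article gives no matching figure for email, opening a message is not completing a survey, and it also reports that 64% of Text4Hope survey respondents favoured email messaging. A difference is plausible, not shown.
- A reader might conclude that the assistant certainly sees the arm. The article does not say who types the ID on a call or what is on the assistant's screen.

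Failed matching from mistyped IDs is at most minor, since the coordinator enters the address or number on the delivery platform at enrolment and entries can be checked against it.

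**Conclusion.** The concern holds as a built-in risk, not as an established bias. Sending survey invitations by the randomised channel ties outcome response to the strategy under test, for PHQ-9, WHO-5, GAD-7, satisfaction and self-reported reading. Under the assumed rates the shift toward email is about 0.025 to 0.20 SD before the fallback. The article states no noninferiority margin, so this cannot be expressed as a share of one. The direction depends on two unverified assumptions: that email loses more patients, and that those lost score worse.

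The arm-revealing identifier is a stated feature of the plan. That it unmasks the assistant is an inference, confined to telephone-assisted assessments; the other outcomes are self-completed by patients who know how their messages reach them. Its effect on the estimate cannot be sized from the article. The change is worth making because it is cheap and the required access is already an eligibility condition.

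**What to change.** 1. Send every survey invitation and reminder by both text and email in both arms.
2. Put an arm-neutral study number in each personalised survey link, replacing the typed address or phone number, and have the telephone assistant work from that number alone.
3. Report response and mode of completion (online or telephone-assisted) by arm at weeks 6, 12 and 24.

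The cost is a survey-platform setting plus, per participant, three survey invitations and any reminders on the non-assigned channel, none carrying supportive content. Since data collection began in April 2021, any change should start in both arms on the same recorded date.

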### Intervention and Implementation Strategies

A research coordinator will assist participants who have provided written informed consent to enroll in either the email messaging or text messaging program by inputting their email address or phone number into the online email messaging or text messaging platforms that will be used to deliver the daily messages. Starting a day after enrollment, participants will receive either daily supportive text messages or daily supportive email messages. Both the email and text messages have the same content and have been crafted by mental health therapists, clinical psychologists, psychiatrists, and mental health service users based on cognitive behavior therapy principles. Each message will be scheduled to be delivered to the participants’ mobile phone or email address at 10 AM MT, and each participant will receive the messages for 6 months.

### Conceptual Framework

This hybrid trial will evaluate and compare both the effectiveness of each STEM strategy (supportive text messaging and email messaging) as well as context, process, and outcomes of the implementation. The trial will integrate two implementation science frameworks to guide the evaluation:

The RE-AIM (Reach, Effectiveness, Adoption, Implementation, and Maintenance) framework [43], which comprises five domains, will be used to assess external validity and feasibility of scale-up.The Consolidated Framework for Implementation Research (CFIR) [43,44] will be used to systematically assess contextual factors (barriers and facilitators) that influence the adoption and implementation of the strategies. The CFIR guides the evaluation of contextual influences on intervention implementation and consists of five domains: intervention characteristics, outer setting, inner setting, characteristics of individuals, and process of implementation.

Figure 1 is an illustration of the evaluation framework of the STEM trial, while Table 1 is an overview of the outcome measures.

**Figure 1 figure1:**
[figure not shown]
Conceptual framework of the *Supportive Text vs Email Messaging* (STEM) trial informed by the RE-AIM (Reach, Effectiveness, Adoption, Implementation, and Maintenance) and Consolidated Framework for Implementation Research frameworks. PHQ-9: Patient Health Questionnaire-9, WHO-5: 5-item World Health Organization Well-Being Index, GAD-7: Generalized Anxiety Disorder-7.

**Table 1 table1:** Overview of the *Supportive Text vs Email Messaging* (STEM) outcome measures.

RE-AIM^a^ domain and outcomes			Measures		Data source		Timeline (months)										
						1-3		4-6		7-9		10-12		13-15		16-18	
**Reach**																	
	Dose delivered	The frequency of emails and text messages sent to the subscribers (including delivery failures)		STEM metadata		✓		✓		✓		✓		✓		✓	
	Dose received	The average number of times participants read the emails or text messages		Survey questionnaire						✓		✓		✓		✓	
**Effectiveness**																	
	Depression symptom score	Patient Health Questionnaire-9 (PHQ-9)		Clinical questionnaire						✓		✓		✓		✓	
	Patients’ quality of life	5-item World Health Organization Well-Being Index (WHO-5)		Clinical questionnaire						✓		✓		✓		✓	
	Anxiety symptom scores	Generalized Anxiety Disorder-7 (GAD-7)		Clinical questionnaire						✓		✓		✓		✓	
**Adoption**																	
	Acceptability/uptake	The number of subscriptions to the text and email services		STEM metadata												✓	
	Acceptability/uptake	Barriers and facilitators		Qualitative focus group discussions guided by the CFIR^b^												✓	

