### Study Aims and Objectives

The *Supportive Text vs Email Messaging* (STEM) trial aims to evaluate comparatively the implementation and impact of two implementation strategies (text messaging and email messaging) for delivering supportive messages to patients with MDD.

The specific objectives are outlined below:

Implementation evaluation:To compare the impact of both strategies for delivering the daily supportive messages on implementation outcomes (adoption, fidelity, reach, cost, sustainability);To evaluate contextual factors that could inhibit or facilitate the implementation of each strategy.Clinical effectiveness evaluation:To compare the mean difference in Patient Health Questionnaire-9 (PHQ-9) [35] scores from baseline and at 6, 12, and 24 weeks for patients with MDD receiving standard care plus daily supportive email messages to those receiving standard care plus daily supportive text messages;To compare the quality of life using the 5-item World Health Organization Well-Being Index (WHO-5) [36] at baseline and at 6, 12, and 24 weeks for patients with MDD receiving standard care plus daily supportive email messages to those receiving standard care plus daily supportive text messages;To compare anxiety levels using the Generalized Anxiety Disorder-7 (GAD-7) scale [37], at baseline and at 6, 12, and 24 weeks, as well as the dropout and satisfaction rates between patients in the two treatment arms.

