### Sample Size

Based on the effect sizes (Cohen *d* of 0.85 and 0.67) achieved in 2 previous randomized trials (n<80 for each trial), which compared daily supportive text messages plus treatment as usual with treatment as usual alone for the management of patients with MDD, a sample size of 80 is estimated to have sufficient power for the current protocol. Allowing for a projected maximal 20% overall dropout rate, we propose to recruit 100 patients with MDD into the trial, with 50 patients randomly allocated into each study arm.

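### The subscription count listed under Adoption is fixed near 50 v 50 by the randomisation, so it cannot compare uptake of email and text

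*Protocol article*

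**What the plan says.** Under Study Aims and Objectives, the first implementation objective of the protocol article is "To compare the impact of both strategies for delivering the daily supportive messages on implementation outcomes (adoption, fidelity, reach, cost, sustainability".

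Table 1 gives Adoption two rows, both labelled as acceptability or uptake and both ticked only for months 16-18. One is a count from trial metadata: "The number of subscriptions to the text and email services". The other is qualitative: focus groups on barriers and facilitators.

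Four statements elsewhere determine what the count can be:

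- **Inclusion Criteria:** every participant must be able to use both channels.
- **Randomization and Blinding:** the trial uses "computer-generated block randomization to ensure balance (1:1) between the two treatment groups", carried out as each participant signs consent.
- **Sample Size:** 100 patients are to be recruited, "with 50 patients randomly allocated into each study arm".
- **Intervention and Implementation Strategies (Methods):** "A research coordinator will assist participants who have provided written informed consent to enroll in either the email messaging or text messaging program", by entering the phone number or email address into the relevant platform.

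Two neighbouring measures also matter. Table 1 places dropout from subscription data under Maintenance (Sustainability), and delivery failures under Reach (Dose delivered). Under Implementation Evaluation, Data Collection, acceptability is also to be measured quantitatively, by user satisfaction questionnaires at 6, 12 and 24 weeks in both arms.

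**The concern.** A count of subscriptions measures uptake when people are free to subscribe, as in an open text-messaging programme. In this trial the service is assigned and the trial's staff set up the subscription, so the count reports the allocation. It has no denominator, such as those offered or those allocated, that would let it vary with uptake.

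At stake is one quantitative measure serving the first implementation objective. The article says its findings should inform implementation at scale and may support policy. Two near-equal counts under the label of adoption could be taken as evidence that email and text are taken up equally, when they only show that the randomisation worked.

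**Working it through.** **1. Reproduce the planned numbers.** Sample Size states that "a sample size of 80 is estimated to have sufficient power for the current protocol" and then inflates it: "Allowing for a projected maximal 20% overall dropout rate".

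80 / (1 − 0.20) = 100, which is 50 per arm at 1:1.

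This matches the plan. The 80 was not tested as a power figure, because this point does not depend on it.

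**2. Count as initial subscriptions.** Each randomised participant gives one subscription on the assigned platform, so the count per service equals the number randomised to it. A departure from 50 v 50 at a total of 100 needs an incomplete last block. The article gives no block size, so these are assumptions:

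| Block size | Complete blocks hold | Left over | Most uneven split of the remainder | Largest imbalance |
|---|---|---|---|---|
| 2, 4, 10 or 20 | 100 | 0 | none | 50 v 50 |
| 6 | 96 (48 v 48) | 4 | 3 v 1 | 51 v 49 |
| 8 | 96 (48 v 48) | 4 | 4 v 0 | 52 v 48 |

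The difference is 0 to 4 subscriptions, and none of it comes from adoption. Eligibility requires access to both channels, so access does not separate the arms either.

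**3. Count as subscriptions still active at the end.** The tick in months 16-18 might suggest this reading. For a given follow-up time the count per arm would be 50 × (1 − dropout in that arm). With assumed dropout of 10% v 30%:

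50 × 0.90 = 45 and 50 × 0.70 = 35.

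The count now moves, but only with dropout, which Table 1 already reports as Sustainability. Messages also stop six months after each person's own enrolment, so a count taken in calendar time would mix retention with enrolment dates.

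**4. Result.** Under the first reading the measure is constant by design. Under the second it repeats another domain. Neither compares adoption.

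**The case against.** The strongest reply is that Adoption does not rest on this count alone. The second Adoption row is a focus-group evaluation, with invitations to people who stayed and people who dropped out. Acceptability, which is part of the label on both rows, is surveyed by arm at three time points, and satisfaction rates are a secondary outcome. The count is a descriptive process figure: no hypothesis, sample size or ANCOVA depends on it, and few readers would be surprised by 50 v 50 in a 1:1 trial.

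Most of this stands, and it limits the point. A reader might infer that the trial will report equal adoption whatever patients think of the two channels, or that the whole Adoption domain is empty. The documents do not support that, because the focus groups and the survey both record what patients think.

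A reader might also try to calculate how few participants would still be receiving messages in months 16-18. The article gives no enrolment period or pattern, so any such percentage would be conjecture. The tick there may simply mark end-of-study collation, since the focus-group and Sustainability rows are ticked in the same column.

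The reply does not rescue the count itself. Focus groups cannot give a numerical comparison of uptake, and Table 1 does not list the survey under Adoption. A few participants might never be successfully enrolled after allocation, which would move the count slightly, but the article defines no measure of that. Nor is this detail left to a fuller document: the measure is stated, and the stated design fixes its value.

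**Conclusion.** The concern holds for the subscription count and no further. As planned, the count is 50 v 50, with at most 51 v 49 or 52 v 48 at the assumed block sizes of 6 and 8, and it cannot support the stated comparison of email with text on adoption. This rests on reading the count as initial subscriptions, one per randomised participant. If it means active subscriptions, it restates dropout.

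The qualitative Adoption row, the acceptability survey and all effectiveness outcomes are unaffected. The change should be made because the measure serves a stated objective and is cheap to replace, but it does not threaten the trial's main conclusions.

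**What to change.** In Table 1, stop using the raw subscription count as a comparative measure; it can remain as a description of participant flow. Replace it with per-arm proportions among all randomised, each with a between-arm difference and 95% CI, from data already collected. For example:

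- the proportion with a successfully activated, deliverable subscription at a fixed time after their own enrolment;
- the acceptability results at 6, 12 and 24 weeks from the user satisfaction survey, with non-respondents shown. Outcome Measures lists satisfaction rates at 12 and 24 weeks only, so the time points should be aligned.

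State how the first measure differs from dropout under Sustainability and delivery failure under Reach. Setting it soon after enrolment would make it a measure of initial activation and not of retention.

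Optionally, record channel access and willingness to use each channel among patients approached, as a descriptive item. It measures stated willingness before allocation, so it does not compare the delivered strategies. It will be missing for patients already screened, as data collection began in April 2021.

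The cost is a table edit, a small extra analysis and some overlap with the Sustainability measure. Precision will be modest. If 80% in each arm met the definition (an assumption, borrowed from the 20% dropout allowance), the 95% half-width for the difference would be 1.96 × √(2 × 0.8 × 0.2 / 50) = 1.96 × 0.08 ≈ 0.16, or about 16 percentage points. The result should be reported as an estimate and not as proof of equal adoption.
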